#### Secondary outcomes

The Physical Functioning Scale of the Brazilian version of the Medical Outcomes Short-Form Health Survey (SF-36) will be used to measure physical health [57]. The Physical Functioning Scale presents ten questions; each one is scored from 1 to 3 according to the perceived limitation [58]. The final score of the scale is calculated according to the orientation of the SF-36 authors ranges from 0 to 100, with lower scores indicating higher limitations [58].

Pain will be measured by the visual analog scale with numerical (0–10) and color gradations [59]. Health-related quality of life will be measured by the Brazilian version of EuroQol-5D (EQ-5D-3L). This instrument evaluates the patient’s current health status in five dimensions (mobility, self-care, usual activity, pain/discomfort, and anxiety/depression). EQ-5D-3L also includes a visual analog scale to record overall health status [60]. The results of this instrument are widely used in economic evaluations [61].

Performance perception and satisfaction will be measured by the Canadian Occupational Performance Measure (COPM) [62]. In this study, only the self-care area will be used. The participant lists the self-care activities they have difficulty performing, chooses the one they consider the most important, and ranks their performance and performance satisfaction from 0 to 10. Higher scores indicate better performance and performance satisfaction.

### Economic evaluation

The economic evaluation will be carried out from the perspective of society and the Brazilian public healthcare system during the study period. The costs will be reported based on values updated to the year of data collection. In this phase, all information will follow the recommendations of the Brazilian Ministry of Health’s Methodological Guidelines for Economic Evaluation [63]. Cost measures will be obtained by estimates of health service utilization (public and private) due to the health condition that caused the referral to outpatient physical therapy and/or generated adverse events. The app development costs will be excluded.

The costs to the public healthcare system will be measured based on the use of health services and procedures reported by participants by the weekly Google form platform, and these data will only be assessed by researchers blinded to group allocation. The costs for hospital care, elective consultations, outpatient or home physical therapy, and medication will be included. These costs will be valued using standardized cost tables of the Brazilian public healthcare system.

Costs to society will include direct costs to participants and caregivers and loss of productivity. The calculation of direct expenses, such as medication, purchase of equipment, transportation, hiring caregivers, and health services will be based on surveys answered by participants. The cost of transportation will be evaluated by the distance between the participant’s home and the physical therapy site, adjusted by the type of transportation used and the price of gasoline. Information on the loss of productivity will be obtained for participants and non-contracted caregivers (e.g., family members) through surveys administered to participants who will indicate whether they have paid work, income from this work, and lost workdays due to the health condition.

The cost-consequence approach will be used to compare the results obtained by the participants in the primary and secondary outcomes with the costs for the two perspectives of analysis (society and public healthcare system). In the cost-utility analysis, the costs for the public healthcare system will be compared with the quality-adjusted life years (QALY) gained from the intervention, obtained by applying the EQ-5D-3L. Sensitivity analyses will be conducted to explore any degree of uncertainty in the estimates, such as sampling, time horizon, discount rate, and imputation of missing data.

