**Methods:**

This is a pragmatic randomized controlled clinical trial with two groups: telerehabilitation and control. Participants (n=230) will be recruited among individuals discharged from hospitals who are in the public healthcare system physical therapy waiting lists. The telerehabilitation group will receive a smartphone app with a personalized program (based on individual’s functional ability) of resistance, balance, and daily activity training exercises. The intervention will be implemented at the individuals’ homes. This group will be monitored weekly by phone and monthly through a face-to-face meeting until they start physical therapy. The control group will adhere to the public healthcare system’s usual flow and will be monitored weekly by telephone until they start physical therapy. The primary outcome will be a physical function (Timed Up and Go and 30-s Chair Stand Test). The measurements will take place in baseline, start, and discharge of outpatient physical therapy. The economic evaluations will be performed from the perspective of society and the Brazilian public healthcare system.

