The exercises will be available in a smartphone app developed for this study. This technology is widely used, being the main form of Internet access [47]. The app will be installed on either the participant’s or the companion’s smartphone. After each exercise, the participants will report their level of pain and difficulty on the app, on a scale of 0 to 5. The exercise program may also be accessed via a computer if the participant prefers this device. After the initial evaluation, participants and their companions will be trained in how to use the app and perform the exercises. Information on deconditioning and the benefits of the proposed exercises will also be provided.

Two previously trained physical therapists who have a master’s degree will be responsible for monitoring the intervention. The proposed exercises and activities will be performed at home, in the presence of a companion to increase the safety of the exercises and facilitate the management of the app. Participants will be monitored by telephone and in-person meetings. The phone calls will take place weekly to monitor the exercise execution, pain, and adverse events. The progression of the exercises’ difficulty through the protocol’s sublevels will be based on this information, as well as those reported daily in the app. The face-to-face meetings will occur monthly (between 24 and 30 days) at the participant’s rehabilitation center. In these meetings, the professionals will evaluate the execution of the exercises and adjust the difficulty level according to the participant’s performance. The intervention will cease when the participant is contacted to begin outpatient physical therapy. Therefore, the participation period in the trial will depend on the waiting time of each participant.

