### Control group

CG participants will follow the usual flow of the waiting list of patients awaiting outpatient physical therapy in the public healthcare system and will not receive any guidance or exercise, as recommended in pragmatic studies. They will be monitored weekly by telephone call to check the onset of outpatient physical therapy and adverse events. Like the TG, the period each CG participant will spend in the trial will depend on the time awaiting outpatient physical therapy. Participants in both the TG and CG will not be prohibited from receiving others interventions such as exercises on their own, physical activity (e.g., walking), medications, or physical therapy elsewhere while on the waiting list, but this information will be recorded.

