### Data collection

Figure 2 shows the schedule of enrollment, interventions, and assessments (according to the SPIRIT). Outcomes will be assessed by in-person meetings at baseline (t0), at the end of the telerehabillitation protocol (t1), and after discharge from outpatient physical therapy or within 6 months of outpatient treatment (t2). All evaluations will be performed by a trained evaluator blinded to group allocation. All instruments show adequate validity and reliability for older adults [48–52].

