**Fig. 2 Fig2:**
[figure not shown]
Schedule of enrolment, interventions, and assessments (according to SPIRIT)

In the baseline (t0), besides the outcomes, socio-demographic and clinical data will be collected, as well as data on the companion, and information on the use of communication technologies.

In the second evaluation (t1), satisfaction with the intervention and the TG app will also be evaluated. To minimize sample loss, the second evaluation will occur before the start of outpatient physical therapy or up to 1 week after the start of physical therapy treatment. The start of the outpatient physical therapy will be accompanied by weekly phone calls to both groups.

The final evaluation (t2) will take place on the last day of outpatient physical therapy or up to 1 week after discharge. The evaluation will consist of the collection of outcomes and information about outpatient physical therapy. Reasons for program discontinuity and follow-up losses will be recorded throughout the study.

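### The economic evaluation has no common time horizon: each participant's window closes around discharge from physical therapy, so any difference between arms in time to discharge feeds into QALYs and costs

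*Protocol article*

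**What the plan says.** The Economic evaluation section sets the window: "The economic evaluation will be carried out from the perspective of society and the Brazilian public healthcare system during the study period". Its plan for cost-utility reads as follows: "the costs for the public healthcare system will be compared with the quality-adjusted life years (QALY) gained from the intervention, obtained by applying the EQ-5D-3L". Time horizon appears there once, in a list of topics for sensitivity analysis, without values.

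The length of the study period is individual. For the telerehabilitation group (TG): "Therefore, the participation period in the trial will depend on the waiting time of each participant". For the control group (CG), "the period each CG participant will spend in the trial will depend on the time awaiting outpatient physical therapy".

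The end of the period is described three ways:

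- Abstract, Methods: "The measurements will take place in baseline, start, and discharge of outpatient physical therapy".
- Data collection, opening paragraph: the last assessment falls "after discharge from outpatient physical therapy or within 6 months of outpatient treatment (t2".
- Data collection, last paragraph, after Figure 2: "The final evaluation (t2) will take place on the last day of outpatient physical therapy or up to 1 week after discharge".

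No EQ-5D-3L assessment is described after t2. The Data analysis plan recognises that time in the study is uneven, but only as a reason for the model chosen for the outcome comparisons.

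**The concern.** A QALY is utility multiplied by time, so a participant followed for less time accrues fewer QALYs at the same health state. Uneven waiting times matter less here: the wait is set by the list, and randomisation should balance it on average. The end of the window is different, because discharge from therapy comes after randomisation and the intervention could bring it forward or delay it.

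If TG participants are discharged sooner, they stop accruing QALYs while alive and possibly at their best utility, and CG participants continue to accrue. Their other costs, such as hospital care and medication, also stop being counted. If TG participants stay in therapy longer, the distortion runs the other way. Cost-effectiveness is a stated aim of the trial, so a QALY difference of the wrong sign would be a serious error in a main result.

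**Working it through.** The article gives no utilities, therapy durations, QALYs or costs, so there is no figure to reproduce. All utilities and durations below are assumptions, used to show size and direction.

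**1. Loss per month of shorter follow-up.** Loss = utility / 12.

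- Utility 0.60: 0.60/12 = 0.050 QALY
- Utility 0.70: 0.70/12 = 0.058 QALY
- Utility 0.80: 0.80/12 = 0.067 QALY

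**2. Constant utility, unequal follow-up.** Own-period QALYs = utility × months/12. CG utility is 0.70. Differences are TG minus CG, and the common horizon is CG's time to t2.

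| Months to t2, TG / CG | Both at 0.70, own periods | TG at 0.75, own periods | TG at 0.75, common horizon | TG gain needed to break even |
|---|---|---|---|---|
| 5 / 6 | -0.058 | -0.038 | +0.025 | 0.14 |
| 8 / 9 | -0.058 | -0.025 | +0.038 | 0.0875 |
| 7 / 9 | -0.117 | -0.088 | +0.038 | 0.20 |
| 6 / 9 | -0.175 | -0.150 | +0.038 | 0.35 |

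First row: 0.70 × 5/12 - 0.70 × 6/12 = 0.292 - 0.350 = -0.058. With the gain, 0.75 × 5/12 - 0.350 = -0.038. On a common 6 months, 0.05 × 6/12 = +0.025. Break-even gain is 0.70 × (6/5 - 1) = 0.14. With no true difference and utilities from 0.60 to 0.80, the range is -0.050 to -0.067 for 5 against 6 months and -0.150 to -0.200 for 6 against 9.

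**3. Utility changing over time (trapezoids).** Both arms start at 0.60, wait 3 months and leave therapy at 0.70. At the start of therapy TG is at 0.65 and CG at 0.60. TG has 3 months of therapy and CG has 4.

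- TG, own period: 0.625 × 3/12 + 0.675 × 3/12 = 0.15625 + 0.16875 = 0.3250
- CG, own period: 0.60 × 3/12 + 0.65 × 4/12 = 0.1500 + 0.2167 = 0.3667
- Difference: -0.042

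Carry 0.70 forward to 9 months:

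- TG: 0.3250 + 0.70 × 3/12 = 0.5000
- CG: 0.3667 + 0.70 × 2/12 = 0.4833
- Difference: +0.017

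The sign reverses.

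**4. Same utilities, equal therapy.** With 3 months of therapy in both arms, CG accrues 0.1500 + 0.65 × 3/12 = 0.3125. The difference is 0.3250 - 0.3125 = +0.0125, the right sign. The distortion comes only from the difference in time to discharge. In this example the own-period sign flips once CG therapy is longer by 0.0125 / (0.65/12) = 0.23 month.

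**5. The two t2 definitions.** They give the same date for courses that finish within 6 months. For an assumed 8-month course, one closes the window at 6 months of therapy if its 6-month phrase is read as a limit, and the other closes it at 8 months or up to a week later. At utility 0.70 that is 0.70 × 2/12 = 0.117 QALY for the same patient.

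**The case against.** The strongest reply is that the article never says QALYs will be summed over unequal personal windows. It does not describe interpolation, extrapolation or adjustment for follow-up length, and a condensed article may leave these to a full economic analysis plan. It also commits to national guidelines for economic evaluation and lists time horizon among the sensitivity analyses. Much of this is fair: silence on the QALY formula is no finding. But the article is not silent on the window. It states one, and its other sections make that window personal and tie its end to discharge. An unspecified sensitivity analysis leaves the base case on that window, and a general reference to guidelines does not settle which end date applies.

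The second reply is that nothing in the article shows the arms will differ in time to discharge. The stated hypothesis is less deconditioning during the wait and lower costs, not shorter therapy. This stands, and it makes the point conditional.

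A reader might infer that the arm discharged sooner must show fewer QALYs and lower costs however much it benefits. The documents do not support that. A large enough utility gain outweighs the lost time, as the break-even column shows. Fewer therapy sessions are a real saving that the analysis should count; the artefact is limited to QALYs and other costs after discharge that go uncounted.

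**Conclusion.** The point holds in conditional form. As written, the economic window differs by participant and ends at an event that treatment could affect. If time to discharge differs between arms, the loss to the arm discharged sooner is about 0.05 to 0.07 QALY per month at assumed utilities of 0.60 to 0.80. That exceeds a true utility gain of 0.05 in every unequal scenario tabulated. If time to discharge is equal, the bias is zero. The documents supply neither the utilities nor the durations, so neither the size nor the direction in this trial can be stated.

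The mismatch between the two t2 descriptions needs no assumption. It affects only courses longer than 6 months, and a reader should not take it as evidence of the QALY bias; it is a separate inconsistency about where the window ends.

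**What to change.** - Set one base-case horizon from randomisation for all participants, long enough to cover the expected wait plus the reconciled t2 limit. Nine months (3 + 6) is only an example: the 3-month wait is a background figure for the city, not a trial rule, and the Discussion expects lists may lengthen.
- Reconcile the descriptions of t2 in the Abstract and Data collection.
- Compute QALYs by interpolating EQ-5D-3L between visits, with a stated carry-forward rule from t2 to the horizon.
- State a rule for costs after t2 over the same window. Carrying a utility forward supplies no costs.
- Vary the horizon and both post-t2 rules in the time-horizon sensitivity analysis already planned.

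The cost is mainly wording in the analysis plan. The downside is an extrapolation assumption for utilities and costs after t2. Observing post-t2 costs instead would mean continuing the weekly cost form to the horizon, which is extra data collection.

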**Fig. 1 Fig1:**
[figure not shown]
Flow diagram

The inclusion criteria are (1) older adults age ≥ 60 years [42], (2) being on a waiting list for outpatient physical therapy in the public healthcare system for any specific medical condition, (3) have recently been discharged from the hospital, (4) no impediment to unload weight in the lower limbs to perform the telerehabilitation program, (5) walking independently or with the aid of a device and being able to sit and stand up from a chair to perform physical function tests, (6) being in a stable clinical condition to avoid complications during the telerehabilitation program, (7) having a smartphone device with Internet access (their own or a companion’s) for the telerehabilitation intervention, and (8) having a companion during the execution of the exercises at home to ensure the safety of the intervention.

The exclusion criteria are (1) the presence of clinical complications that make physical exercise impossible; 2) neurological disease, such as Parkinson or stroke; (3) a score in the Mini-Mental State Exam less than 13 for people with no schooling, 18 for individuals with low/moderate schooling, and 26 for people with a high level of schooling [43]; and (4) not being able to understand instructions or complete the tests. Excluded individuals will receive a booklet on the importance of staying active while awaiting physical therapy.

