### Telerehabilitation intervention

The TG will receive a multi-component intervention that includes resistance exercises targeting the main muscle groups of the lower and upper limbs, and balance exercises. There are strong recommendations for the use of this type of intervention, showing improvement in clinical outcomes in older adults, such as reducing falls and increasing muscle strength and mobility [2, 17–19, 44, 45]. These exercises are easy to perform, do not require special equipment or accessories, and were designed for execution without professional supervision. In addition, the participant will choose an activity from their daily routine that they have difficulty in performing and hope to improve in the short term. The participants’ choosing an activity is a strategy aimed to stimulate engagement in the intervention and increase of their independence.

The exercise program will be carried out three to five times a week with high intensity, as suggested by Falvey et al. (2015) [2]. The volume will have three series; the number of repetitions will be customized based on Borg’s Modified Perceived Exertion Scale [46], with effort levels ranging from five to seven. The exercises’ difficulty levels and their sublevels of progression are shown in Table 1 and Additional file 2. Each participant may carry out the entire exercise program once a day or intermittently, two or three times a day (Table 1).

**Table 1 Tab1:** Exercise description and progressions

EXERCISE	DESCRIPTION	PROGRESSIONS	
**Multiplanar single leg balance reach**	The participant starts this exercise in the standing position, assume single lower limb support, and move the opposite lower limb forward, to the side and backward as far as possible and maintaining the knee as straight as possible. The participant performs 3 series of 8 to 15 repetitions in each direction.	**Basic level**	1. The participant is only allowed single upper limb support on a wall or a stable surface (e.g. table or chair) for balance. The participant is allowed to touch the floor with the forefoot of the swing limb at the longest reach distance.
			2. Same as basic level 1, but with increased number of repetitions (minimum increase of 2 repetitions in each direction).
			1. Same as basic level 2, but the participant increases swing limb reach distance.
		**Moderate level**	2. Same as basic level 3, but the participant is not allowed upper limb support.

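### The productivity items, as worded, miss unpaid and part-day companion time that telerehabilitation itself requires, so part of its societal cost goes uncounted

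*Protocol article*

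**What the plan says.** The protocol article, under Economic evaluation, takes two perspectives: society and the Brazilian public healthcare system. On the first it states: "Costs to society will include direct costs to participants and caregivers and loss of productivity". The direct expenses are described by examples, "such as medication, purchase of equipment, transportation, hiring caregivers, and health services will be based on surveys answered by participants". For productivity loss, which covers participants and caregivers who are not hired, the surveys ask about paid work, the income it brings and "lost workdays due to the health condition". Unlike the direct expenses, these items are given as a definition and not as examples.

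Inclusion criterion 8 (Setting and participants) requires "having a companion during the execution of the exercises at home to ensure the safety of the intervention". The section Telerehabilitation intervention repeats this for the treated arm: "The proposed exercises and activities will be performed at home, in the presence of a companion". It adds that companions help with the app and are trained after the initial evaluation. On frequency: "The exercise program will be carried out three to five times a week with high intensity". A day's program may be done in one go or split into two or three bouts, and the intervention runs until the participant is called for outpatient therapy. Under Control group, controls receive no guidance or exercise.

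Societal costs enter the cost-consequence comparison. The cost-utility analysis sets QALYs against public healthcare system costs only.

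**The concern.** The productivity items carry three restrictions: the work must be paid, the unit is the workday, and the loss must be attributed to the health condition. Companion time at exercise sessions can fail each of them. The companion may have no paid job, a session takes part of a day, and the time is spent because of the program. The design assigns this recurring family input to one arm only.

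The trial's hypothesis includes a reduction in costs. If families supply time that the survey does not record, an apparent societal saving could partly reflate to work moved onto the companion. The sensitivity analyses named as examples (sampling, time horizon, discount rate, imputation of missing data) do not address this. Hours that were never asked about cannot be properly recovered at the analysis stage, so the forms have to ask for them.

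**Working it through.** The document states no figure for companion time, session length, wages, caregiver employment or societal cost, so there is no plan figure to reproduce on this point. The check has three parts.

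**1. What the items cover, as worded**

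| Companion situation | Captured? |
|---|---|
| Hired companion | Yes, under direct expenses |
| Direct expenses of the caregiver | Yes, under direct costs |
| Employed relative loses a full workday | Possibly, if the respondent attributes it to the health condition |
| Employed relative loses part of a day | Not as worded; the unit is workdays |
| Relative without paid work | No |

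**2. Size of the companion input the program requires**

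Inputs from the document: 3 to 5 sessions a week (Telerehabilitation intervention); a wait of up to 3 months (Background), which is 3 × 52 / 12 = 13 weeks; 115 participants per group (Sample size). Assumption, not in the document: 20 to 60 minutes per session.

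Sessions = weeks × sessions per week. Hours = sessions × minutes / 60.

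- Sessions over 13 weeks: 13 × 3 = 39 to 13 × 5 = 65.
- Low end: 39 × 20 / 60 = 13 hours, or 13 / 8 = 1.6 eight-hour days.
- High end: 65 × 60 / 60 = 65 hours, or 65 / 8 = 8.1 eight-hour days.
- At 30 minutes: 39 × 0.5 = 19.5 to 65 × 0.5 = 32.5 hours.
- For a 4-week wait: 12 × 20 / 60 = 4 to 20 × 60 / 60 = 20 hours.
- Whole arm, if everyone waited 13 weeks: 13 × 115 = 1,495 to 65 × 115 = 7,475 hours.

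The protocol requires no such hours in the control arm. These figures assume full adherence and leave out the one-off companion training.

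**3. What this implies for the difference between arms**

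Let h be session hours per telerehabilitation participant, and let c_T and c_C be other unpaid care hours per participant in the telerehabilitation and control arms. All three are unmeasured to the extent that they are unpaid and cost no full paid workday. If all hours carry the same value, the omitted part of the incremental cost (telerehabilitation minus control) is

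h + c_T − c_C.

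The term h alone is positive, so leaving it out understates telerehabilitation's cost. The total reverses sign if controls need more than h extra hours of other unpaid care. Per week of waiting, h runs from 3 × 20 / 60 = 1 hour to 5 × 60 / 60 = 5 hours. An excess of 1 to 5 hours a week of unpaid help to controls would therefore cancel it. The document gives no figure for c_T or c_C.

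**The case against.** The strongest reply has four parts.

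- **The items are not as narrow as they look.** Societal costs include direct caregiver costs and hired caregivers, and unpaid caregivers are asked about lost work. Since the exercise follows from the condition that led to referral, a respondent could report a lost day under it. This stands. A reader might infer that the survey counts only lost paid workdays or cannot detect companion time at all; the text does not support either.
- **Net bias is not shown.** The same items leave out unpaid care of controls. If telerehabilitation limits deconditioning, as hypothesised, controls may need more help at home. They may also exercise or attend therapy elsewhere, possibly accompanied. This stands too. A reader might infer that the societal comparison is biased toward telerehabilitation, but the document supports only the direction of the one omitted component.
- **Pricing only lost paid work is a costing convention, and a co-resident companion may give up little.** This is a fair argument about the value per hour, and the reason to report a zero-value analysis. It is not a reason to leave the hours unrecorded.
- **The article condenses a questionnaire that is not shown.** The full survey may already ask for hours, in which case checking it settles the matter. The article does, however, state the productivity items as a definition, and followed as written they leave the gap.

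The consequence is also limited: neither the primary outcome nor the cost-utility analysis depends on these items.

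**Conclusion.** The point holds in a narrow form. The stated productivity items do not capture unpaid or part-day companion time that the intervention requires and the control arm is not assigned. That omission, taken by itself, understates telerehabilitation's societal cost in the cost-consequence comparison. The net direction of any bias remains open.

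The size is illustrative: about 13 to 65 companion hours per telerehabilitation participant at the longest stated wait, and less for shorter waits or incomplete adherence. It rests on an assumed session length and cannot be turned into money from the document. Nor does anything in the document show that companion time is the largest input families supply. The change is worth making before data collection because it is cheap then and cannot properly be made good afterwards.

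**What to change.** In both arms, in the same wording and over the same period:

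1. Add to the weekly form one item on total unpaid caregiver hours, covering all informal care and including time spent accompanying exercise. Asking only about exercise sessions would replace one asymmetry with another, because it would leave unpaid care of controls uncounted. A single total also helps keep allocation hidden from the blinded researchers who assess the form's data.
2. Reword the lost-work item to hours or days lost because of the health condition or because of taking part in the study program.
3. Report societal costs with these hours valued at an hourly rate stated in advance, whether or not the caregiver has paid work, and at zero as a sensitivity analysis.

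The cost is one added item and one reworded item on forms already in use, and a line in the economic analysis. The form becomes slightly longer, and the societal result for telerehabilitation may be less favourable.
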